The primary objective of this study is to investigate the characteristics of oxygenation in the central cortex and upper-limb flexors during grasping tasks in individuals with stroke. fNIRS systems will be used to simultaneously assess blood flow dynamics in the central cortex and upper-limb flexors during grasping tasks, evaluating the heterogeneity of muscle oxygenation activity in the upper-limb flexors and analyzing the activation levels of cerebral cortex functional areas. The secondary objective is to explore the hemodynamic alterations in the cerebral cortex and flexor muscles of the affected upper limb during grasping tasks, induced by the combination of VR and conventional rehabilitation therapy, to attempt to investigate the rehabilitation mechanisms of upper limb motor function in individuals with stroke. Participants with stroke will undergo a combined intervention of VR training and conventional rehabilitation therapy. Changes of hemodynamic in cerebral cortex and upper limb flexor hemodynamics, as well as upper limb motor function, will be evaluated before and after the intervention. Furthermore, correlations between each parameter will be analyzed to gain insights into the relationship between VR training, neuronal activity, and upper limb motor function in stroke patients.

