## Methods and design

### Study design

This study follows a longitudinal non-randomized controlled design to examine the synchronous oxygenation characteristics of the central cortex and upper-limb flexors during a grasping task in stroke patients with varying levels of grasp function.

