### Participants

Inclusion Criteria:

1.First stroke confirmed by CT or MRI.2.Medically stable.3.Age between 40 and 80 years.4.Onset of stroke occurred between two weeks to three months.5.Right handedness.6.No severe cognitive impairment (MMSE ≥ 22 points) and able to follow motor commands.7.Able to maintain an upright position in an armless seat for at least 30 min.8.Modified Ashworth grade of the affected upper limb is equal to or less than grade 2.9.Brunnstrom motor function grade of the affected hand is equal to or greater than grade 3, and able to grasp a 2.5cm3 wood block with effort.10.Patient and their family members agree to participate in the study and have signed the informed consent.

Exclusion Criteria:

1.Unstable clinical condition.2.Presence of any neuropsychiatric illness other than stroke.3.Diagnosis of schizophrenia, bipolar disorder, obsessive-compulsive disorder, personality disorder, or major depression.4.Presence of skin lesions or infections on the upper limb.5.History of upper limb fractures, deformities, or finger absence.

Sample Size:

Based on the sample size of previous studies (Huo et al., 2019a), a total of 60 patients following stroke will be enrolled in this study, with 20 patients in each of the three groups.

Group A: Patients who can only grasp and lift a 2.5 cm^3^ wooden block with their hemiplegic hand.Group B: Patients who can grasp and lift 2.5 cm^3^ and 5 cm^3^ blocks with their hemiplegic hand but cannot lift 10 cm^3^ blocks.Group C: Patients who can pick up 2.5 cm^3^, 5 cm^3^, and 10 cm^3^ wood blocks with their hemiplegic hand but exhibit abnormalities in speed and coordination during the task.

In addition, a control group of 20 age-matched healthy subjects without neurological diseases or history of upper limb trauma will also be enrolled.

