### Experimental procedure

All stroke participants will undergo a comprehensive assessment both before and after the intervention. The assessment will involve the use of fNIRS to simultaneously monitor the blood oxygen parameters of the cerebral cortex and upper limb flexors during a grasping task. Additionally, pre- and post-intervention assessments will include the Action Research Arm Test (ARAT), the upper extremity section of the Fugl-Meyer Assessment (FMA-UE), the Modified Ashworth Scale (MAS), MyotonPRO, and the Modified Barthel Index (MBI).

During the intervention period, all stroke participants will receive 30 min of VR training and 30 min of occupational therapy once a day, five times a week, for a total of three consecutive weeks. Figure 1 shows the study procedure.

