### Statistical analysis

Before conducting parametric tests, several steps were taken to prepare and analyze the data. Outliers were identified using normal Q–Q plots and box plots, and data points that were more than three standard deviations from the mean were considered outliers and subsequently excluded from the analysis (Minati et al., 2011). Missing values were addressed using multiple imputation analysis to estimate and replace the missing data points (Blankers et al., 2010).

Descriptive statistics were used to summarize the demographic and clinical characteristics of the study participants. The normality of the data distribution was assessed using the one-sample Kolmogorov-Smirnov test. For comparisons between different groups, chi-square tests were used for categorical variables, while independent t-tests were used for continuous variables.

To evaluate the differences in outcome measures before and after the intervention for participants with stroke, paired sample *t*-tests were employed. The correlations between variables were assessed using either the Pearson correlation coefficient (r) or the Spearman correlation coefficient (ρ), depending on the nature of the data.

The significance of interregional coupling strength between the resting state and different grasping states was evaluated using a one-way analysis of variance (ANOVA). Additionally, χ^2^ tests were utilized to identify statistically significant differences in interregional coupling direction between the resting state and different grasping states.

All statistical analyses were performed using SPSS software (version 20.0; SPSS Inc., Chicago, IL, USA). All tests were two-tailed, and a significance level of *p* < 0.05 was considered statistically significant.

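### Pre-post change is tested with paired t-tests that carry no grasp-level term although patients are enrolled in fixed quotas of 20 per level; a model of change on group costs 2 df and supplies the joint test of change by level that is not named

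*Protocol article*

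**What the plan says.** Under Participants, the sample is set by quota: "a total of 60 patients following stroke will be enrolled in this study, with 20 patients in each of the three groups". The groups are ordered by grasp ability. Group A is "Patients who can only grasp and lift a 2.5 cm^3^ wooden block with their hemiplegic hand"; B adds the 5 block and C adds the 10 block. The number is justified as "Based on the sample size of previous studies", with no effect size, standard deviation or power.

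Under Experimental procedure, the treatment is the same in every group: "all stroke participants will receive 30 min of VR training and 30 min of occupational therapy once a day, five times a week". Among treated patients, grasp level is therefore the only design factor.

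The Statistical analysis section gives the pre-post test as "To evaluate the differences in outcome measures before and after the intervention for participants with stroke, paired sample" t-tests. It does not say whether these pool all 60 patients or are run within each group. The same section assigns independent t-tests to comparisons of continuous variables between groups, without saying that these include change scores. One-way ANOVA is named only for coupling strength between the resting and grasping states. All tests are two-sided at 0.05.

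**The concern.** A design factor fixed at enrolment normally belongs in the analysis. When stratum sizes are set in advance, differences between strata in mean change are not sampling error of the overall mean change, yet a plain paired t-test on the pooled sample counts them as error. Running the test separately in each group avoids this. It leaves 19 error degrees of freedom per group, and three separate p-values do not show whether the groups differ.

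Two things are at stake. One is some power for the overall pre-post result, in a study whose Limitations section already calls the sample relatively small. The other is a direct answer on whether change depends on grasp level, which the 3 x 20 structure could give from data already collected.

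**Working it through.** **Inputs from the article.** Three groups of 20 (3 x 20 = 60, which agrees with the stated total); two-sided 5%; paired t-test. The figure of 20 per group cannot be re-derived, since no effect size, SD or power is given.

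**Assumed inputs.** Within-group SD of change = 1. Group mean changes are m - g, m and m + g, with g from 0 to 1. The article gives neither the SD nor g.

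**Step 1: standard error if the 60 are pooled.** A paired t-test is a one-sample t-test on change. The between-group sum of squares from the means is 20 x (g² + 0 + g²) = 40g². The plain variance has 59 df and expectation (59 + 40g²)/59; the within-group variance has 57 df and expectation 1. The ratio of plain to stratified SE is therefore √(1 + 40g²/59). The share of the variance in change explained by group is R² = (2g²/3)/(1 + 2g²/3).

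**Step 2: effect on the pooled test.** Type I error and power come from simulation (40,000 runs per setting). Power is at a mean change of m = 0.37 within-group SD.

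| g | R² | SE ratio | Type I error, plain | Power, plain | Power, stratified |
|---|---|---|---|---|---|
| 0 | 0 | 1.000 | 0.051 | 0.81 | 0.81 |
| 0.25 | 0.04 | 1.021 | 0.045 | 0.80 | 0.81 |
| 0.5 | 0.14 | 1.081 | 0.033 | 0.76 | 0.81 |
| 0.75 | 0.27 | 1.175 | 0.022 | 0.69 | 0.80 |
| 1.0 | 0.40 | 1.295 | 0.011 | 0.61 | 0.80 |

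The stratified test stays at about 0.05 throughout.

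**Step 3: the same effect on the scale of total SD.** Set the mean change at 0.368 total SD, where the plain test with n = 60 has 80% power. The stratified test uses 0.368/√(1 - R²) with 57 df. By the noncentral t distribution, power is 84% at R² = 0.10, 86% at 0.143 and 90% at 0.25. At R² = 0 it is 0.800 against 0.801 for the plain test, so the 2 df cost almost nothing.

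**Step 4: if the test is run within each group.** With n = 20 and 19 df, 80% power needs a change of 0.660 SD. Using the error pooled over the three groups (57 df) raises power at that effect to 83%, if the variance of change is equal across groups.

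**Step 5: a test of change by level.** A one-way ANOVA of change on group has 2 and 57 df and noncentrality 40g². Its power is 26% at g = 0.25, 79% at g = 0.5 and 99% at g = 0.75. If the independent t-tests were instead applied to change, there would be three pairs. Treated as independent, their familywise error is 1 - 0.95³ = 14%.

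**The case against.** The strongest reply is that a paired t-test is a valid test of pre-post change. A reader might infer that the planned standard errors are simply too wide. The article does not support that as a fact. It needs the 60 to be pooled, which is not stated, and mean change to differ by grasp level, which is unknown. Pairing already removes baseline differences between the groups. Where inflation does arise, the test is conservative, so no false positives follow.

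A reader might also infer that the study was set up to compare change across grasp levels. The Study design phrase "in stroke patients with varying levels of grasp function" belongs to a clause about oxygenation characteristics during the task, not about change. The secondary objective, "The secondary objective is to explore the hemodynamic alterations in the cerebral cortex and flexor muscles of the affected upper limb during grasping tasks", concerns what the combined therapy induces and does not ask whether that differs by level. It would also be wrong to say that the article offers no between-group test at all, since the independent t-tests could be applied to change scores. Nor does anything in it plan to read a difference from one group reaching significance and another not.

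Finally, stratum terms are often left to an analysis plan. Here, however, the article names its tests purpose by purpose and assigns this purpose a test without the design factor.

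All of this limits the point without removing it. The independent t-tests are not tied to change and take two groups at a time, and the better analysis needs no new data.

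**Conclusion.** The point stands as a low-cost improvement, not as an error that invalidates a result. The stated pre-post test omits the factor on which enrolment is fixed, and no joint test of change by grasp level is named.

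The loss is conditional. With pooling, the standard error is about 2%, 8% or 30% too wide for differences of 0.25, 0.5 or 1 within-group SD between adjacent levels. At 0.5 SD, power is 0.76 instead of 0.81. With equal change the loss is nil. Without pooling there is no inflation, and the gain from a shared error term is about 3 percentage points (80% to 83%). A 2-df test would have about 79% power at 0.5 SD, so the planned sample could address the question if the difference is moderate.

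All sizes rest on assumed SDs and evenly spaced mean changes. They also treat the quotas of 20 as fixed, with the average over the three groups as the quantity of interest.

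**What to change.** In Statistical analysis, replace the paired t-tests, for each outcome, with a model of change on group (A, B, C), or equivalently a mixed model with visit, group and visit-by-group. Report:

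- the change averaged over the three groups, with its within-group standard error;
- the change in each group, with its confidence interval;
- the 2-df visit-by-group test.

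Allow unequal variances across groups if the data call for it. With 20 per group the standard error of the average is the same either way: (1/9)(s²_A + s²_B + s²_C)/20 equals the mean of the three variances divided by 60. What the allowance affects is the group-specific intervals, the joint test and the degrees of freedom.

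For fNIRS, base this model on the 2.5 block. According to fNIRS data acquisition and analysis, it is the only block that all 60 patients grasp.

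Label between-group differences in change exploratory, because the groups are not randomised and are formed on baseline ability.

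The cost is 2 degrees of freedom and a change of wording. The data are already planned, and SPSS has the procedures. The change also settles whether the pre-post result is pooled or by group.

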### fNIRS data acquisition and analysis

The fNIRS data acquisition process is illustrated in Figures 2, 3. The participants were seated comfortably in an adjustable chair within a quiet room. For participants in Group A, they were instructed to grasp a 2.5 cm^3^ wooden block first with their unaffected hand and then with their affected hand. Participants in Group B performed two sets of tests, grasping a 2.5 cm^3^ wooden block and a 5 cm^3^ wooden block, using their unaffected hand first and then their affected hand. Subjects in Group C were asked to sequentially pick up three blocks of different sizes, again using their unaffected hand first and then their affected hand. The control group was required to grasp and lift three different sizes of cubic wooden blocks, first with their right hand and then with their left hand.

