**FIGURE 3 F3:**
[figure not shown]
Blood oxygen parameters of cerebral cortex and upper limb flexors are synchronously detected during the grasping task.

Before the actual data collection, a practice session was conducted to familiarize participants with the tasks. The fNIRS data collection followed a block design paradigm. Each condition was preceded by 50 s of rest, which served as a baseline period to stabilize the fNIRS signal. Between each condition, participants were allowed a 2-min break. Each condition consisted of three blocks, with each block consisting of a 20-s motor task period followed by a 20-s rest period. During all rest periods, participants were instructed to keep their focus still on the handle of the ARAT toolbox.

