### Outcomes

#### Primary outcomes

In this study, two different applications of functional near-infrared spectroscopy (fNIRS) were employed: fNIRS of the cerebral cortex and fNIRS of the upper-limb flexors.

For fNIRS of the cerebral cortex, a Huichuang portable 35-channel fNIRS system was utilized to measure blood oxygen parameters, including HbO, HbR, and HbT. The system used the continuous wavelet transform method to calculate the wavelet amplitude (WA) of signals ranging from 0.01 to 0.08 Hz in each cortical region (Huo et al., 2019a). The phase information was extracted from the signals. The inter-hemispheric lateral degeneration index was then calculated based on WA to evaluate the degree of brain activation transfer from the affected side to the healthy side. Additionally, the extracted phase information was used for effect connection analysis based on dynamic Bayesian inference to assess the strength of the interaction between the cerebral cortex regions (Huo et al., 2019a).

For fNIRS of the upper-limb flexors, a portable muscle oxygen detector called OctaMon from Artinis Medical Systems B. V. was employed. This system utilized an 8-channel near-infrared spectroscopy setup to measure blood oxygen parameters (HbO, HbR, HbT) in the flexor muscles of the upper limb. A distribution map was created based on the measured parameters. The spatial-temporal parameters of blood oxygen were analyzed to evaluate muscle activities.

Overall, both fNIRS applications aimed to investigate blood oxygen parameters in different regions of interest (cerebral cortex and upper-limb flexors) and analyze their characteristics to understand brain activation transfer, cerebral cortex interactions, and muscle activities in the context of the study.

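### The rest and grasping states come from the same participants, but coupling strength and direction are compared with a one-way ANOVA and chi-square tests that, as named, ignore the pairing; the main cost is lost power

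*Protocol article*

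**What the plan says.** The Statistical analysis section of the protocol article gives two tests for comparing rest with the grasping states. For strength: "The significance of interregional coupling strength between the resting state and different grasping states was evaluated using a one-way analysis of variance (ANOVA". For direction, χ² "tests were utilized to identify statistically significant differences in interregional coupling direction between the resting state and different grasping states". It names no repeated-measures, mixed-model or paired categorical method for either comparison. The same section does name pairing for the pre/post comparison: "To evaluate the differences in outcome measures before and after the intervention for participants with stroke, paired sample" t-tests.

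The section on fNIRS data acquisition and analysis shows where the states come from. Under Figure 3: "Each condition was preceded by 50 s of rest, which served as a baseline period to stabilize the fNIRS signal", with "each block consisting of a 20-s motor task period followed by a 20-s rest period". Group A grasps one block size and Group B two. For the rest, "Subjects in Group C were asked to sequentially pick up three blocks of different sizes" and "The control group was required to grasp and lift three different sizes of cubic wooden blocks". Everyone does the tasks with each hand in turn.

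The outcome is not peripheral. Primary outcomes includes "effect connection analysis based on dynamic Bayesian inference to assess the strength of the interaction between the cerebral cortex regions".

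**The concern.** No state is recorded in a separate set of people. Whether the resting state means the 50 s baseline or the 20 s rest periods, it comes from the same person in the same session as the grasping data. A between-subjects one-way ANOVA treats the states as different people, so stable differences between persons stay in the error term although they cancel from the state contrast. A chi-square test on direction does the same with paired categories.

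What is at stake is the sensitivity of a primary outcome. The block design provides a within-person contrast, and the named tests do not use it. The Limitations section already warns that the small sample can affect power.

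**Working it through.** **Inputs from the article.** 20 participants per group; two-sided 0.05; number of states k (rest plus block sizes, one hand) = 2 for Group A, 3 for Group B, 4 for Group C and controls. The sample size rests on precedent, so there is no power figure to reproduce.

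**Assumptions (not in the article).** Normal data with total variance 1; equal correlation ρ between any two states of one person; all grasping states shifted 0.5 SD from rest; ρ = 0.4, 0.6, 0.8.

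**Why the one-way test is conservative within a group.** With no state effect, the expected mean square for states is 1 − ρ. The one-way ANOVA divides it by an error mean square with expectation 1. The repeated-measures ANOVA divides it by one with expectation 1 − ρ. The one-way ratio is therefore centred near 0.6, 0.4 and 0.2 instead of near 1, and the test has its nominal size only at ρ = 0.

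**Power with repeated measures.** The noncentrality is λ = n Σ(μ_j − μ̄)² / (1 − ρ) = 20 × 0.5² × [(k − 1)/k] / (1 − ρ), with k − 1 and 19(k − 1) degrees of freedom.
- k = 2: λ = 2.5/(1 − ρ) = 4.17, 6.25, 12.5
- k = 3: λ = 3.33/(1 − ρ) = 5.56, 8.33, 16.67
- k = 4: λ = 3.75/(1 − ρ) = 6.25, 9.375, 18.75

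The one-way figures come from simulation (40,000 runs per setting, standard error at most 0.25 percentage points).

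| States | ρ | One-way: type I error | One-way: power | Repeated measures: power |
|---|---|---|---|---|
| 2 | 0.4 | 1.3% | 30% | 49% |
| 2 | 0.6 | 0.3% | 27% | 66% |
| 2 | 0.8 | <0.1% | 22% | 92% |
| 3 | 0.4 | 1.0% | 26% | 51% |
| 3 | 0.6 | 0.2% | 21% | 70% |
| 3 | 0.8 | <0.1% | 14% | 95% |
| 4 | 0.4 | 0.8% | 22% | 51% |
| 4 | 0.6 | 0.1% | 15% | 70% |
| 4 | 0.8 | <0.1% | 9% | 95% |

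Repeated-measures type I error was 4.8% to 5.1% throughout. Independent simulations of the same settings agree to about one percentage point.

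**Direction, two states, n = 20** (8,000 runs; binary direction from a latent normal variable with correlation 0.3, 0.5, 0.7; assumed latent shift 0.8 SD). Type I error was 2.4%, 1.1% and 0.5% with chi-square, against 4.5%, 4.2% and 4.7% with McNemar. Power was 49%, 47% and 47% against 51%, 58% and 70%. At correlation 0.3 the loss is slight; it grows with the correlation.

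**When the error could turn anti-conservative.**
- *Several rows per person and state* (four states, one-way ANOVA, no state effect). Under the model above, entering 2, 3 or 6 rows leaves type I error below 1% at ρ = 0.4 and 0.6. It rises only if persons also differ in their response to each state. With half of the within-person variance of that kind, 6 rows give about 31% (ρ = 0.4) and 16% (ρ = 0.6), but 2 rows still give less than 5%.
- *Pooling Groups A to C.* One observation per person and state gives rest 60, 2.5 cm³ 60, 5 cm³ 40 (B and C) and 10 cm³ 20 (C only). If groups differ by g per level with no state effect, the state means are g, g, 1.5g and 2g, so block size carries severity. False rejection is 24–28% for an assumed g = 0.5 SD, 4–8% for 0.3 SD and below 1% for no group difference (ρ = 0.5 and 0.7).

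**The case against.** The strongest defence is that one-way counts factors, so a one-way repeated-measures ANOVA is also one-way. The article condenses a fuller plan, and its authors use paired t-tests elsewhere, so they know about pairing. This reading cannot be excluded for the strength outcome, and a sentence confirming it would settle that half. But the section says paired where it means paired and does not do so here. The chi-square test has no such reading. Nor is this a detail left to a fuller document: a test is named, and as named it does not fit the stated design.

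The error is also in the safer direction. Within a group the named tests give fewer false positives, not more, and the article sets no power target that they would break. That stands, and it limits the point to lost power. The effect size and correlations are assumptions, and four states apply only to Group C and the controls; for Group A the gap is smaller at each correlation, though still large.

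A reader might go further and infer that entering hands or time windows as extra rows makes the test anti-conservative. The article does not say that rows are entered this way, and extra rows alone do not have that effect. It takes several rows together with substantial person-by-state variance. Inflation from pooling the stroke groups is likewise conditional: the article does not say that they are pooled, and the size depends on how far the groups differ.

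**Conclusion.** The concern holds. The tests named for a primary connectivity outcome do not reflect the within-person design: certainly for direction, and for strength unless a repeated-measures ANOVA was meant. Within a group the consequence is a conservative test. At correlations from 0.4 to 0.8, power for a 0.5 SD shift falls by roughly 19 to 70 percentage points for two states (49 − 30 = 19; 92 − 22 = 70) and 29 to 86 points for four (51 − 22 = 29; 95 − 9 = 86). These sizes rest on the assumed shift, correlations and equal-correlation model. What does not depend on the chosen shift is that the one-way test has its nominal size only at zero correlation, which is unlikely for recordings from one person in one session. The documents do not support a claim that the plan as written produces false positives. The wording should be corrected before analysis, because the outcome is primary and the change is cheap.

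**What to change.** **Strength.** Replace the one-way ANOVA with a linear mixed model that has a participant random effect and state and hand as within-person factors. Fit it within each group. If it is fitted across groups, add group as a between-person factor and limit group-by-state contrasts to the block sizes that each group performs: Group A has no 5 or 10 cm³ data and Group B no 10 cm³ data, so a complete-case repeated-measures ANOVA over all states and groups would not work. Code hand as affected/unaffected in patients and right/left in controls. Within one group a sphericity-corrected repeated-measures ANOVA is acceptable. If several windows per person and state are kept, average them or add a participant-by-state random effect.

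**Direction.** Use a GEE or mixed logistic model clustered on participant. Within one group, McNemar (two states) or Cochran's Q (three or more) will do.

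State whether each comparison is made within a group or across groups. If repeated-measures ANOVA was meant all along, say so; the chi-square tests still need replacing.

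**Cost.** A little more analysis work than a change of wording, because of the empty group-by-size cells. No new participants, visits or recordings.
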